#### Randomization procedures and methods to minimize bias

Eligible patients were randomly assigned to the COS intervention or TAU in a ratio of 1:1. An electronic randomization list was generated using Randlist 1.2 as a random generator. Unique randomization numbers were generated to ensure that the study arm assignment was unbiased. Randomization was stratified for two infant age groups (4–6 months vs. 7–9 months) and separate random lists were created for each age group. Block sizes of six to eight were used for the randomization of the treatment arms. The randomization list was generated by the randomization representative and was stored in a password-protected electronic document accessible only by the randomization representative. Each random number was stored in a concealed randomization envelope. After a patient’s eligibility for the study was determined, the next available randomization number was assigned to the patient, in ascending order. To minimize bias that could have arisen from knowledge of treatment allocation, all outcome assessors were blind to treatment allocation and a random sample of outcome measures was re-rated by independent assessors.

### Statistical methods

#### Sample size and power

The primary outcome for treatment efficacy is the rating of quality of child attachment at follow-up at children’s age 16–18 months (COS vs. TAU) by an objective rater blind to treatment allocation. Differences in distributions of the quality of child attachment (secure vs. insecure-avoidant, -resistant, -disorganized) between both treatment modalities are calculated by a chi-square test of significant statistical independence. A power analysis for comparing COS and TAU with a power of 80% and the probability of making a Type I (α) error of 5%, with a medium effect (*W* = 0.3) suggested a recruited sample size of N = 80.

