**Methods/Design:**

This randomized controlled clinical trial tests whether promoting attachment security in infancy with the Circle of Security (COS) Intervention will result in a higher rate of securely attached children compared to treatment as usual (TAU). Furthermore, we will determine whether the distributions of securely attached children are moderated or mediated by variations in maternal sensitivity, mentalizing, attachment representations, and psychopathology obtained at baseline and at follow-up. We plan to recruit 80 mother-infant dyads when infants are aged 4-9 months with 40 dyads being randomized to each treatment arm. Infants and mothers will be reassessed when the children are 16-18 months of age. Methodological aspects of the study are systematic recruitment and randomization, explicit inclusion and exclusion criteria, research assessors and coders blinded to treatment allocation, advanced statistical analysis, manualized treatment protocols and assessments of treatment adherence and integrity.

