[71,72], which represents the emotional organization of relationships and the basis for defensive processes in the parent–child interaction. The need for relationships and the fear of the loss of these relationships or separation play central roles in this. Each mother’s idiosyncratic manifestation of this complex interplay was taken into consideration in the selection of the video sequences.

Every therapeutic group consisted of six women. Six groups were planned and realized for this trial. The infants did not participate in group sessions, and childcare was provided for them while the mothers were in sessions.

The treatment manual, which was designed for parents with children aged 0–5 years, combines psycho-educational and therapeutic modules (e.g., video analyses in the group), focusing on attachment, exploration, communication and affective experiences between parent (in this study, mother) and child, aiming to help the mothers to elaborate their strengths and struggles in order to create a haven of safety and a secure base for their children. Guided by the treatment manual, there is a shift from predominantly observing behavioral and affective cues of both mother and child to gaining more insight into maternal thoughts and feelings and their defensive nature (“shark music”) with regard to the attachment and autonomy needs of the children, with the goal of overcoming their impact on child-mother attachment formation and maternal sensitivity. This is intensified by showing video segments of the “linchpin struggle” of each mother-infant dyad.

The 90-minute-COS group sessions took place weekly. Two therapists facilitated each group. Treatment adherence and integrity in this study was assured by weekly supervision of the therapists with [name], one of the originators of the COS intervention.

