### Primary outcome

For the primary outcome, that is, child attachment security (vs. insecurity) as a categorical variable, differences of the proportions of child attachment security between TAU and COS treatment arms will be estimated by a chi-square test of statistical significance.

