### Limitations

The circumstances of this clinical trial necessitated some scientific compromises. One limitation of this trial is that the person who oversaw the implementation of the COS intervention is also the principle investigator. Thus, personal factors (allegiance effects) may limit the generalizability of our findings. In view of the fact that the study sample comprises clinically referred mothers with mental disorders and their infants, it is ethically unacceptable to use a no-treatment control group. Therefore, in the best interest of our patients we have used TAU as the control intervention to which patients are randomized. According to the natural flow of patients attending the outpatient unit, eligible women with infants participated voluntarily, and, having given their informed consent, were randomly assigned to COS or TAU. Thus, our clinical sample varied in terms of psychopathology. There may be a sampling bias, insofar as the mothers with infants attending the outpatient unit might represent a more severely mentally disordered sample choosing to participate in this trial. This may limit the generalizability of the findings, due to sampling bias and a lack of true representativeness. Hence, replication studies or a multi-site trial are necessary. A sample size of N = 80 was determined before any data were collected, based on the assumption of medium effect size and power. For practical reasons, we defined a sample size of N = 72, such that 36 mother-infant dyads were randomly assigned to COS (six COS therapeutic groups) and 36 mother-infant dyads to TAU. Further long-term follow-up measures might be useful to capture positive changes of the intervention that may be attributable to a sleeper-effect
[66] and apparent only at later follow-up stages.

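### The article claims 80% power at N = 80, but 72 dyads were randomised, which gives about 72–75% power for W = 0.3 before any drop-out

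*Protocol article*

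**What the plan says.** Under Sample size and power, the protocol article gives the inputs as a chi-square test, W = 0.3, alpha 5% and 80% power, and says that these "suggested a recruited sample size of N = 80". The abstract (Methods/Design) repeats 80 dyads, "with 40 dyads being randomized to each treatment arm".

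The Limitations section gives a different size. It records that 80 was fixed before data collection and continues: "For practical reasons, we defined a sample size of N = 72", with 36 dyads randomised to each arm. The description of the COS intervention agrees. Each group had six women, and "Six groups were planned and realized for this trial", so 6 × 6 = 36 COS dyads.

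The primary analysis (Statistical methods, Primary outcome) is a chi-square test on "child attachment security (vs. insecurity) as a categorical variable, differences of the proportions of child attachment security between TAU and COS treatment arms". That is a 2×2 table with 1 df. No power figure for 72 dyads appears anywhere in the article.

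**The concern.** There are two problems. First, the stated inputs do not return the stated N when put through the formula that belongs to W. Second, the only power figure in the article is attached to a size that the trial did not randomise.

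What is at stake is how a null result is read. A non-significant primary comparison would be judged against a one-in-five chance of having missed the planned effect, when the design as carried out had a larger one. That effect is already big in absolute terms. With equal arms and 50% secure overall, W = 0.3 means 35% versus 65% secure.

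**Working it through.** **Inputs.** From Sample size and power: chi-square test, W = 0.3, alpha 0.05, power 0.80, N = 80. From Randomization procedures: 1:1 allocation. From Primary outcome: binary outcome, so 1 df. From Limitations: N = 72, 36 per arm.

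**Step 1: the plan's own figure.** For a chi-square test the noncentrality is λ = N × W². At 1 df, 80% power at alpha 0.05 requires λ = (1.960 + 0.842)² = 7.849. Hence N = 7.849 / 0.09 = 87.2, which rounds up to 88 (44 per arm). The stated 80 is 8 short.

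**Step 2: power at each size.** Power is 1 − F(3.84; 1 df, λ), with F the noncentral chi-square distribution function.

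| N | λ = 0.09 N | Power |
|---|---|---|
| 88 | 7.92 | 80.4% |
| 80 | 7.20 | 76.5% |
| 72 | 6.48 | 72.1% |

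**Step 3: exact check.** The W formula is a large-sample approximation, so the uncorrected Pearson test was also enumerated exactly over two binomials. Pooled secure rates ran from 0.3 to 0.6, with the arms set so that W = 0.3.

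- 40 per arm: 77.7–79.5%.
- 36 per arm: 72.0–74.6%, so the chance of missing the effect is 25.4–28.0%.

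**Step 4: can another standard method give 80?** The alternatives tried at W = 0.3 were:

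| Method | N for 80% power | Power at 80 | Power at 72 |
|---|---|---|---|
| Two-sided, pooled two-proportion | 86 | 77.6% | 73.0% |
| Two-sided, arcsine | 84–86 | not computed | not computed |
| Two-sided, continuity-corrected | 98–100 | 70.3–72.4% (exact) | 63.1–65.3% (exact) |
| Two-sided, unpooled variance | 80 | 80.3% | 76.1% |
| One-sided 5%, no correction | 69 | 85.0% | 81.6% |
| One-sided 5%, continuity-corrected | 80–82 | not computed | not computed |

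The unpooled figure can be followed by hand at 35% versus 65%: n per arm = 7.849 × (0.35 × 0.65 + 0.65 × 0.35) / 0.30² = 7.849 × 0.455 / 0.09 = 39.7, so 40. An unpooled calculation may therefore be where 80 came from, but it is not the power of the chi-square test that the article names.

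**Step 5: effect detectable with 80% power.** W = 2.802 / √N, which is 0.313 at N = 80 and 0.330 at N = 72.

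**Step 6: missing outcomes (assumption only).** The Strange Situation is taken only at follow-up (Table 1), so a lost dyad adds nothing to the primary test. The article gives no loss rate. If 5–20% of the 72 were lost, the W-formula power would be 69.9–62.4%.

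**The case against.** The strongest reply is that 80 is nearly right. Exact power at 40 per arm is within about 0.5 to 2.3 points of target, one standard approximation returns 80, and the article names no software or formula. This stands. The gap at N = 80 is modest, and a reader who inferred a gross calculation error would be going too far. It does not rescue 72, where every two-sided method for which power was computed gives less than 77%.

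A second reply is that the cut to 72 is disclosed. It is, openly, as a compromise under Limitations, so there is no ground to infer concealment. What is not disclosed is the cost in power, and the abstract still describes 40 per arm as randomised.

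A third is that the hypothesis is directional and a one-sided 5% test would reach 80% with 72. The article states no one-sided test, and the chi-square test it names is non-directional.

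Two stronger readings should be resisted:

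- The sample-size text speaks of distributions and lists "secure vs. insecure-avoidant, -resistant, -disorganized", so a reader might infer a four-category test with a much larger required N. The Aims and hypothesis section, the definition of the primary outcome and the primary analysis are all secure versus insecure. The list is best read as naming the insecure subtypes.
- A reader might treat power in the 60s as established, or the lack of a drop-out allowance as a defect in itself. No loss rate is given, and a condensed article may leave that allowance to the full protocol. With complete data, 28% is the upper end of the risk of missing the effect, not its floor.

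**Conclusion.** The point holds in this form. The stated 80% power does not follow from the stated inputs at N = 80, by a small margin: 76.5% on the W formula, about 78–79.5% exactly. It is clearly not delivered at the 72 dyads randomised, where power is about 72–75% with complete follow-up and the chance of missing the planned effect is about 25–28%, not 20%. It would be higher with any missing Strange Situation outcome, by an amount that the article does not allow one to fix.

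This rests on a two-sided 5% level, the binary 1-df test, equal arms, W = 0.3 as planned and, for the exact range, pooled secure rates between 0.3 and 0.6 without continuity correction. The validity of the primary test, its type I error and the treatment estimate are not affected.

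**What to change.** - Keep both sizes on record: 80 dyads planned, 72 randomised (36 per arm, six COS groups of six). The pre-specified 80 should not be erased.
- Correct the abstract where it describes 40 dyads as randomised to each arm.
- Replace the 80% claim under Sample size and power, and add the same sentence under Limitations: for the binary secure versus insecure chi-square test (1 df, two-sided 5%), 72 dyads give about 72–75% power for W = 0.3 before any drop-out, and 80% power only for W of about 0.33.
- If power under drop-out is shown, label the loss rate as an assumption.

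No further enrolment is proposed and no analysis changes. The only cost is a less favourable power statement.

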#### Statistical analysis plan

All available variables will be used without missing outcomes being factored in. The analyses are based upon the assumption of ignorable drop-outs. Characteristics of the treatment groups were assessed at baseline.

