### Assessment and outcomes measures

All measures of pre- and post-assessment are listed in Table 
1.

**Table 1 T1:** Assessments administered at baseline and follow-up throughout the trial

**Time point**	**SSP**	**MBQ-S**	**DIP**	**AAI**	**AAI-RF**	**PRFQ-1**	**SCID-I,-II**	**BDI**	**SCL-90**	**PSI**	**DERS**	**CBCL**	**FBB-E**

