f. Child behavior and emotional problems (CBCL11/2) at follow-up will be analyzed with respect to mean scores in either arm of the trial, using multiple linear regression analyses. Again, maternal psychopathology (BDI, SCL-90) and maternal parenting stress (PSI) will be treated as predictor variables, in addition to treatment modality.

g. Further multiple regression analyses will be conducted, with mean changes in maternal sensitivity (MBQS, DIP), mentalization (RF, PRFQ-1), and maternal attachment representations (positive shift, no/negative shift) before and after treatment, as predictor variables.

h. Binary logistic regression models will be used to compare proportions of child attachment security (vs. insecurity) at follow-up as criterion variables, using treatment modality, maternal sensitivity, maternal self-reflection (RF), maternal psychopathology (BDI, SCL-90), and maternal parenting stress (PSI) as predictor variables.

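### The primary chi-square uses arm and completers only, so it needs drop-out to be ignorable given arm alone, although baseline maternal data that would relax this are collected

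*Protocol article*

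**What the plan says.** The Statistical analysis plan section of the protocol article gives two rules on missing data: "All available variables will be used without missing outcomes being factored in", and "The analyses are based upon the assumption of ignorable drop-outs". It does not say which variables drop-out is ignorable given.

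The Primary outcome part of the statistical methods then states that "differences of the proportions of child attachment security between TAU and COS treatment arms will be estimated by a chi-square test of statistical significance". No covariate and no stratification factor enters that test.

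Table 1 shows the Strange Situation Procedure (SSP) at follow-up only. Maternal sensitivity (MBQ-S), DIP, AAI, reflective functioning (RF), BDI, SCL-90 and PSI are all ticked at baseline. The infant age stratum is known for every randomised dyad.

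Item h of the Secondary outcomes returns to the same endpoint: "Binary logistic regression models will be used to compare proportions of child attachment security (vs. insecurity) at follow-up as criterion variables, using treatment modality", together with sensitivity, RF, BDI, SCL-90 and PSI. It does not say whether these predictors are baseline or follow-up values, and it is not presented as a way of handling drop-out.

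**The concern.** Assuming ignorable drop-out protects an analysis only if the analysis conditions on whatever makes the drop-out ignorable. The primary test conditions on arm and nothing else. It therefore needs completers within each arm to be representative of that arm, or the distortion to be the same in both arms.

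The article itself gives grounds for doubt. Its Background links maternal illness and reduced mentalizing to insecure or disorganized attachment, and says these mothers differ greatly in motivation and compliance. The arms also make different demands. COS is a fixed course of 20 weekly group sessions that starts only once a group of six has been filled. TAU starts at once, varies in intensity with need, and is ended by the mother. Different mothers could be lost from each arm.

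The SSP is taken 7 to 14 months after entry (16 − 9 = 7; 18 − 4 = 14), with no earlier SSP value to draw on. Baseline maternal measures are the natural source of information about missing outcomes, and the primary test uses none of them. At stake is whether a difference in secure rates reflects COS or reflects who came back.

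**Working it through.** **Inputs from the article.** 36 dyads per arm (Limitations); 1:1 allocation; unadjusted chi-square on observed SSP outcomes. There is no drop-out rate, secure rate or covariate association, so there is no figure of the plan's own to reproduce on this point. The sample-size figure is not an input.

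**Assumed inputs (none is in the documents).** One binary baseline risk factor present in half the dyads; secure rate p_m without it and p_s with it, equal in both arms, so there is no treatment effect; retention r_m and r_s by factor level.

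**Formula.** With the factor at 50%, the completers' secure rate in an arm is

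(r_m·p_m + r_s·p_s) / (r_m + r_s),

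and its departure from the true rate is ((p_m − p_s)/2) × (r_m − r_s)/(r_m + r_s). The bias in the comparison is this departure in COS minus that in TAU.

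**Results with p_m = 70% and p_s = 30% (true rate 50%).** Type I error is from 100,000 simulated trials of 36 per arm, two-sided 5%. Loss is shown as without / with the factor.

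| Loss in COS | Loss in TAU | Completers secure, COS vs TAU | Bias (points) | Type I error |
|---|---|---|---|---|
| 20% / 20% | 20% / 20% | 50.0% vs 50.0% | 0 | 5.2% |
| 30% / 30% | 10% / 10% | 50.0% vs 50.0% | 0 | 5.1% |
| 5% / 35% | 5% / 35% | 53.75% vs 53.75% | 0 | 5.2% |
| 5% / 35% | 20% / 20% | 53.75% vs 50.0% | +3.75 | 6.2% |
| 0% / 50% | 25% / 25% | 56.7% vs 50.0% | +6.7 | 8.1% |
| 5% / 35% | 35% / 5% | 53.75% vs 46.25% | +7.5 | 9.1% |

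Fourth row: (0.95 × 0.70 + 0.65 × 0.30) / (0.95 + 0.65) = 0.86 / 1.60 = 0.5375. Swapping the arms reverses the sign, so the bias could also work against COS.

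**Weaker association.** With secure rates of 65% / 35%, COS loss 5% / 35% and TAU loss 20% throughout: (0.95 × 0.65 + 0.65 × 0.35) / 1.60 = 0.845 / 1.60 = 0.528, a bias of +2.8 points. With 60% / 40% and COS loss 10% / 30%: 0.10 × 0.20 / 1.60 = 0.0125, or +1.25 points.

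**Effect of conditioning.** In the last three rows of the table, completers within each factor level are secure at 70% or 30% in both arms. Averaging those over the 50/50 mix of all randomised dyads gives 50% vs 50%, and the bias disappears. It does so completely because the example makes this one factor the only driver of loss.

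**Loss depending on attachment itself, equally in both arms.** Take true rates of 35% vs 65% and retention of 90% if secure, 70% if insecure. Completers show 40.9% vs 70.5%. The difference moves from 30.0 to 29.6 points and the odds ratio stays at 3.45.

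**Reach of the unobserved outcomes.** If 7 of 36 were missing in each arm (assumed), opposite extreme outcomes among them would move the full-sample difference by 7/36 = 19.4 points either way.

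**The case against.** Several stronger readings are tempting, and the document does not support them.

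- *The plan contradicts itself.* A reader might infer that ignorable drop-out and a complete-case chi-square are incompatible. They are not: loss at random within arm is a special case of ignorable drop-out. The plan relies on a stronger form of the assumption than it needs to and does not say so.
- *The comparison is valid only if loss is unrelated to attachment.* That holds for each arm's own secure rate. It is too strong for the comparison, as the third row of the table and the attachment-dependent example show. With no treatment effect, bias in the difference requires a loss mechanism that differs by arm.
- *The baseline data go unused.* This is true only of the primary test. Item h models the same outcome with covariates that are all measured at baseline. With baseline values it would be valid under drop-out ignorable given arm and those covariates. With follow-up values it would adjust for sensitivity and mentalizing, the routes by which COS is meant to work, and would not repair the problem.
- *The lack of a missing-data sensitivity analysis is a defect.* An article commonly leaves this to the full analysis plan, which is not shown. It is not held against the plan here.

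The size is also open to challenge. With about 29 completers per arm, the standard error of the difference is about √(2 × 0.25 / 29) = 0.131, or 13 points. A bias of 2.8 points is then about 0.2 standard errors, with a type I error near 5.5%. The planned effect, W = 0.3, corresponds to about 30 points at a 50% overall secure rate. Imputing by arm from six or more predictors would be fragile at this sample size. All of this stands. It limits how much can be claimed and calls for a small covariate set; it does not make conditioning on arm alone the better choice.

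**Conclusion.** The point holds in a limited form. The rules as written give a complete-case chi-square that conditions on arm only, so the primary comparison depends on drop-out being ignorable given arm, although prognostic maternal measures are collected at baseline. If loss depends on such factors and does so differently in the two arms, the comparison is biased even though drop-out is ignorable given the baseline data. On the assumed inputs the bias runs from about 1 to 7.5 points, with type I error between about 5.5% and 9% where it was worked out. If the loss pattern is the same in both arms, or unrelated to prognosis, there is no bias under the null. The document gives no drop-out rate, secure rate or covariate association, so none of these figures predicts what will happen in this trial. This is an inexpensive improvement to a stated method. It does not show that the primary result will be wrong.

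**What to change.** Keep the chi-square as planned and make four changes.

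1. State that the chi-square assumes drop-out ignorable given arm alone.
2. Add, as the main drop-out-robust analysis of SSP security, one of two options. The first is a logistic model with arm, age stratum and a small pre-specified set of baseline covariates (for example one symptom score, PSI and mini-MBQS), reported as a risk difference standardised over all randomised dyads. The second is multiple imputation of SSP security from the same small set.
3. State in item h that the predictors are baseline values whenever that model is used for the treatment comparison. A model with follow-up values should be labelled as a mediation or association analysis.
4. Add a sensitivity analysis that varies the assumed secure rate among missing dyads separately in COS and TAU, and report where the conclusion changes.

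The cost is wording and modest programming; no new data are needed. The constraint is size: at about 36 dyads per arm before loss, a long covariate list risks overfitting or separation, so the set must stay small and be fixed in advance.
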